### Randomization

To prevent selection bias and insure against accidental bias, we will allocate patients to the treatment groups by randomization. In this way we can expect to get comparable study groups regarding observed and unobserved confounders.

Patients who are suitable after verification of the inclusion and exclusion criteria will be thoroughly informed about the WOPP study by a study physician. After approval of the study and submission of the written informed consent, patients are randomized. Randomization is done electronically via a web-based software tool (SecuTrial, interActive Systems GmbH, Berlin, Germany). We chose an allocation ratio of 1:1 because it maximizes statistical power for a given total sample size and there are no ethical or practical objections to this ratio. To minimize random error, 750 patients are to be screened and 360 patients (*n* = 180 per arm) will be randomized. Twenty centers have declared their participation in the study. The study design is shown in Fig. 1.

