### Sample size estimation

The sample size calculation is based on the primary endpoint PTX recurrence within the first 24 months. We will test the null hypothesis of equal underlying population proportions for PTX recurrence for patients treated with pPTX alone and patients treated by WRPP by using a two-sided Fisher’s exact test at significance level 0.05.

Our assumptions for calculating the sample size are based on Czerny et al. [7]. Conservatively we assume underlying PTX recurrence proportions of 8.6 % for patients under pPTX and 1.4 % for patients under WRPP, a difference of 7.2 %. Sample sizes of 170 for both groups ensure a power of 80 % to detect this difference as a significant deviation from the null hypothesis of equal PTX recurrence proportions for both treatment strategies. Due to the visits without painful procedures and the comparatively young and healthy study population, we assume a low drop-out rate of 5 %. Therefore, 2*180 = 360 patients are to be included in the study at the beginning. PASS 11, developed by NCSS Statistical Software, Kaysville, UT, USA, was used for sample size calculation.

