### Statistical analysis

The primary statistical analysis will be performed in the intention-to-treat (ITT) population. This analysis set includes all randomized subjects for which a diagnostic thoracoscopy has confirmed that thoracoscopic operation is feasible. We assume that the number of patients with recurrent pneumothorax after 24 months follows a binomial distribution in both groups. Within the primary analysis we will test the null hypothesis of equal proportions, which means equal probabilities for recurrent pneumothorax after 24 months for patients subject to WRPP and patients subject to PP by a two-sided Fisher’s exact test. Furthermore, a stratified analysis with the stratification factor study center will be performed using Mantel-Haenszel estimation of relative risk and testing for heterogeneity of stratum risks.

Within a secondary analysis we will calculate an adjusted odds ratio for the experimental treatment method WRPP relative to the comparing treatment PP using multiple logistic regression analysis. Secondary outcome analyses will be carried out depending on scale level and distribution and will be considered exploratory. In our analyses, 95 % confidence intervals will be calculated. The method for constructing the confidence interval in each case will depend on the type of the response variable and the variable to be tested. Controlling for potential confounders (such as age, gender, and smoking) will be performed by using multiple statistical models adjusting for these variables. Additional subgroup analyses considering gender aspects, age, and study center are planned. SAS 9.3 or corresponding subsequent SAS versions will be used for all data analyses.

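### Primary test: Fisher's exact test is valid but conservative for rare recurrences; Boschloo's exact test would keep the 5% cap and gain about 2 to 3 points of power at the planned size

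*Protocol article*

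**What the plan says.** The Protocol article fixes the confirmatory test in two places, and they agree.

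- **Statistical analysis.** "we will test the null hypothesis of equal proportions" of recurrence at 24 months, for "patients subject to WRPP and patients subject to PP by a two-sided Fisher’s exact test". The number of recurrences "follows a binomial distribution in both groups".
- **Sample size estimation.** The same Fisher's "exact test at significance level 0.05", two-sided. The assumed recurrence rates are "8.6 % for patients under pPTX and 1.4 % for patients under WRPP, a difference of 7.2" percentage points. "Sample sizes of 170 for both groups ensure a power of 80 % to detect this difference". A 5% drop-out allowance brings this to 180 per arm, 360 in total. This section calls the pleurectomy-only arm pPTX; I read that as PP.
- **Randomization.** "We chose an allocation ratio of 1:1".

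The article mentions neither the conservatism of Fisher's test at low event rates nor any unconditional exact test.

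**The concern.** Fisher's test computes its p-value as if the total number of recurrences were fixed in advance. Here the arm sizes are set by design, but the total is random under the article's own two-binomial model. At the planned rates about 17 recurrences are expected in 340 patients (170 × 0.086 + 170 × 0.014 = 17). With so few events the attainable conditional p-values lie far apart, and Fisher usually stops well short of 5%.

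Suppose 11 recurrences occur with 170 per arm. A 9 v 2 split gives p = 0.061. The next split, 10 v 1, gives 2 × [C(170,10) × C(170,1) + C(170,11)] / C(340,11) = 0.0105. For that total, Fisher spends about 1% of its 5%.

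At stake is some power on the only confirmatory test. A different exact test would recover part of it from the same patients.

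**Working it through.** **Inputs (Protocol article).** Two-sided alpha 0.05, Fisher's exact test, p1 = 0.086 (PP), p2 = 0.014 (WRPP), 1:1 allocation, 170 per arm evaluable, 180 per arm randomised.

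**1. The plan's own figure.** The normal approximation with continuity correction gives

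z = [d − 1/n − 1.96 × √(2 p̄(1 − p̄)/n)] / √{[p1(1 − p1) + p2(1 − p2)]/n}

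With d = 0.072, p̄ = 0.05 and n = 170: (0.0720 − 0.0059 − 0.0463) / 0.0233 = 0.85, so power is 80.2%. The stated 80% at 170 is reproduced. For drop-out, 170 / 0.95 = 178.9, which is 179 and is rounded to 180.

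**2. Exact power of Fisher.** I enumerated every pair of counts (x1, x2), weighted each by the two binomial probabilities, and added up those with two-sided Fisher p ≤ 0.05. The two-sided p is the sum over tables no more likely than the one observed. Power is 84.7% at 170 and 87.2% at 180 per arm. Fisher reaches 80% at about 155 per arm.

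**3. True type I error of Fisher.** The same enumeration with one common rate in both arms, at 170 per arm:

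| Common rate | Fisher | Boschloo |
|---|---|---|
| 1.4% | 0.75% | 1.8% |
| 3% | 2.0% | 3.1% |
| 5% (mean of the two planned rates) | 2.6% | 3.6% |
| 8.6% | 3.0% | 3.9% |
| Maximum over all rates | 4.1% | 5.0% |

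**4. Boschloo's test.** It uses the Fisher p-value as its statistic. The cutoff is the largest value whose rejection rate stays at or below 5% for every common rate; rates up to 0.5 suffice because equal arms make the problem symmetric. At 170 per arm the cutoff is Fisher p ≤ 0.0614; at 180 it is 0.0576. Both exceed 0.05, so Boschloo rejects whenever Fisher does and cannot be less powerful.

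**5. Power at 8.6% v 1.4%.**

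| Per arm | Fisher | Boschloo | Gain (points) |
|---|---|---|---|
| 180 | 87.2% | 89.2% | 2.0 |
| 170 | 84.7% | 87.8% | about 3 |
| 130 | 70.3% | 75.7% | 5.4 |
| 100 | 55.1% | 60.1% | 5.0 |
| 50 | 15.0% | 26.4% | 11.4 |

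The gain does not change smoothly with sample size, because the cutoff moves in steps. Fisher would need about 183 per arm to match Boschloo at 170, some 13 more per arm.

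**6. Smaller effect, 170 per arm, WRPP at 1.4%.** If PP recurrence is 7%, power is 66.8% (Fisher) v 72.4% (Boschloo). If it is 6%, 51.5% v 58.0%.

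**7. A result near the boundary.** For 9 v 2 recurrences with 170 per arm, Fisher p = 0.061 and Boschloo p = 0.049.

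**8. Enrolment.** The Discussion reports 61 patients randomised by 22.01.2015 and plans the end of recruitment for October 2015. Trial status dates the first patient 19.11.2013. That is 61 in about 14 months, or about 4.3 a month. If that pace held for the nine months or so that remain, the total would be about 61 + 9 × 4.3 ≈ 100, or 50 per arm. Constant pace is my assumption; the Discussion itself expects more than 500 patients from the centres' commitments.

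**The case against.** The strongest reply is that nothing here is broken. Fisher's test is conventional, holds its level, and is named identically for planning and analysis. Its conservatism has already been paid for: exact power is above the 80% target at both 170 and 180 per arm. The trial is also unblinded (Blinding section) and 61 patients had been randomised at the time of writing. Moving to a less conservative test now could look like choosing the test after the fact, for 2 points of power at the planned size.

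Most of this stands. It is why the point is an optional improvement, and why the timing of any change matters. It does not remove the gain when enrolment or the effect falls below plan, and there the margin over 80% no longer helps.

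Three stronger readings are tempting, and the figures do not support them:

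- **That the trial is underpowered because of Fisher.** Under its own assumptions it is not.
- **That Boschloo's test would run at 5%.** It only caps the error at 5%. At a 5% common rate it runs at about 3.6% (170 per arm) or 3.5% (180). At 180 per arm and a 1.4% rate it equals Fisher, at 0.85%.
- **That the gain is larger because only low recurrence rates are plausible.** Maximising over rates up to 20% alone gives a cutoff near 0.067 at 170 per arm. The maximum error of that rule over all rates is 5.75%, so it no longer guarantees 5%.

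**Conclusion.** The point holds as a cheap improvement, not as an error in the plan. Fisher's test is valid but uses about half of its nominal 5% at the planning rates. Boschloo's test keeps the 5% cap, needs no extra patients, and adds about 2 points of power at 180 per arm and about 3 at 170. The gain is larger in smaller samples: about 5 points at 100 to 130 per arm and 11 at 50. Even so, 26.4% power at 50 per arm would not rescue a trial that small.

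These figures assume independent binomial counts, equal arms, recurrence rates of 8.6% and 1.4% unless stated otherwise, and full maximisation over the common rate. Whether enrolment will fall short is not settled by the article; the projection of about 100 patients rests on a constant pace.

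**What to change.** In both Sample size estimation and Statistical analysis, replace the two-sided Fisher's exact test with Boschloo's two-sided exact unconditional test at 0.05. State that the Fisher p-value is the test statistic and that the error is maximised over the whole range of common rates. Report the Fisher p-value as supportive.

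Make the change by a dated amendment before anyone compares outcomes by arm, and record that no such comparison had been made. The planned 360 patients can stay, since Boschloo is never less powerful than Fisher; the exact power at 170 and 180 per arm can be quoted with the amendment.

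The cost is two amended sentences, a validated routine, and a test that is less familiar to readers. If outcomes have already been compared by arm, keep Fisher as primary and give Boschloo as a labelled sensitivity analysis.

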### Study procedure

All patients with pPTX recurrence or a refractory first event will be screened for study participation. For each potential study participant the inclusion and exclusion criteria will be checked by a study physician. After providing informed consent, the participant will be randomized in one study group.

The baseline pain level and the quality of life are determined using the SF-36 questionnaire and the VAS score prior to any other study intervention in all participants. The standard treatment is parietal pleurectomy alone (control arm), and the validating therapy is the parietal pleurectomy in combination with an additional apical pulmonary wedge resection (experimental arm). All surgeries are performed by video-assisted thoracoscopy under general anesthesia and include a parietal pleurectomy for PTX treatment. Additionally, in the experimental group an apical pulmonary wedge resection is performed. The postoperative treatment is carried out according to the respective hospital standard. Perioperative variables like morbidity, mortality, subjective pain, duration of chest tube, surgical reintervention, and length of hospital stay will be determined. To assess the long-term effect of surgical intervention, all patients will be followed up for two years. The examinations for the individual follow-up visits are listed in Table 1.

**Table 1 Tab1:** Overview of the study-related examinations

	Pre-OP	Intra-OP	Station	Follow-up		
Visit	V1		V2	V3	V4	V5
Week/month	OP-X		7. post OP day or day of discharge	6 months	12 months	24 months
Inclusion/exclusion criteria	X					
Consent	X					
Demographic data	X					
Medical history	X					
Smoking	X		X	X	X	X
Physical examination	X					
Chest X-ray^a^	X					
Pain level (VAS)	X		X	X	X	X
Quality of life (SF-36, German version)	X		X	X	X	X
Vanderschueren classification		X				
Postoperative complications			X	X		
AEs/SAEs			X	X	X	X
Duration of hospital stay			X	X		
Material costs^b^						X

^a^In case of pregnancy of a study participant, the chest X-ray will be replaced by a chest ultrasound

^b^At the end of the operation, the number of used trocars and stapling magazines will be documented

### Data management

The patient data are collected using electronic data entry screens (Case Report Forms, eCRFs). The study software complies with the regulatory requirements in accordance with GCP, FDA 21 CFR Part 11, and contains i) audit trail, ii) electronic signature, iii) programmable plausibility, consistency, and range checks, iv) query management system for online monitoring, and v) customizable roles and permissions system. In the study, software pseudonyms for the study data are used. This ensures the strict separation of identifying data (IDAT) and medical data (MDAT) of patients. Medical data are sent without personally identifiable information to the study database and saved there. However, any identifying patient data will be printed at the study center and remain there. The link between IDAT and MDAT can only be carried out by using a key, also called the pseudonym. Each study center maintains a confidential list of all patients, in which the patient numbers are connected with the full patient names. Only the local study team and the monitor will have access to this list. The original files can be viewed by monitors, auditors, and inspectors. The study database is protected by an authentication method. Only authorized study personnel with a personal identifier code will have access to the study database. Individual permission levels and roles are defined. This affords the implementation of different processing modalities of the study data, for example, to unlock certain forms (partial data) for editing, reading, or data control (review). The study database is permanently accessible via the Internet. The study data are recorded online and are transmitted directly into the study database; there is no local data storage. Data transfer between the local computer and the study database occurs via a secure connection (SSL encryption). To ensure data security, study data will be saved by daily backups of the study database. In addition, the availability of the study server is guaranteed by using the professional server environment at the IT center of the Charité University Medicine Berlin. To ensure the quality of the study data, the monitor performs data control during the study period. The originals of all central study documents including documentation forms are kept in the study coordination office (with the lead investigator) for at least ten years after completion of the study. The participating study centers keep the incurred administrative documents (correspondence with ethics committee, study management, study center), patient identification list, the signed consent forms, copies of the documentation forms, and the general study documentation (protocol, Amendments) for the above period. The original data of the study patients (medical records) are kept according to the filing deadline applicable to the study sites, but for no less than ten years.

### Monitoring

The coordination and implementation of the monitoring is performed by the Clinical Trial Center Würzburg (CTCW) at the University Hospital of Würzburg and the Surgical Regional Center (CRZ) Berlin. Here, the compliance with the requirements of the study protocol and ICH/GCP Guidelines are reviewed by the monitors. Each center is visited once before randomization of the first patient (initiation visit). Monitor visits are carried out at appropriate intervals during the study and at study completion. The verification of the correct transmission of data in the medical record into the documentation sheets (100 % Source Data Verification) is performed for the first two patients enrolled in each study center. The monitoring of the core data is performed for every patient. The following is considered as core data: existence of the patient, patient consent, correct inclusion and exclusion criteria, primary outcomes, and serious adverse events according to the protocol.

### Assessment of safety, analysis and reporting

Adverse events (AEs) have been defined as pneumonia, pleural effusion, postoperative bleeding requiring revision, blood loss requiring transfusion, pleural empyema, persistent lung fistula that last longer than five days after surgery, deep vein thrombosis, and wound infection. Serious adverse events (SAEs) are medical occurrences that lead to any of the following: immediately life-threatening situation, re-operation, persistent or significant disability/incapacity, inpatient hospitalization or prolongation of existing hospitalization, admission to an intensive care unit, death. All SAEs and all adverse events AEs are documented and assessed by the investigator and documented in the medical record and in the eCRF, regardless of whether, in the opinion of the investigator, there is a causal relationship with the study conduct or not. The documentation includes the type of event, start, end, expression/severity, causality, and outcome of the incident. Furthermore, the investigator must inform the lead investigator about the occurrence of an SAE within three days after having taking note of it and provide the investigator with a detailed written report (SAE sheet). Fatal or life-threatening SAEs will promptly, meaning within 24 hours, be reported after they are known.

### Data Safety Monitoring Board (DSMB)

An independent data protection committee (DSMB), which consists of three external experts (thoracic surgeon, biometrician, clinical scientist), will be concerned with patient safety and evaluation of benefits and risks. The DSMB examines the data collected and monitors patient safety by evaluation of AEs and SAEs. On the basis of the evaluated data, the DSMB makes recommendations on continuation, modification, or termination of the trial. The DSMB will meet regularly, at least five times during the duration of the study.

### Dropout/exclusions

The termination criteria of the study are defined as thoracic reintervention (for example, drainage system, thoracentesis with suction, surgery due to recurrence or other indication), the patient’s desire to withdraw from the current study, and violation of the protocol. During the hospital stay after surgery (and thus after randomization) a new or additional chest tube is not a termination criterion. Also, a pleural puncture for aspiration of pneumothorax or residual pneumothorax is not a termination criterion. Reoperation during the hospital stay after the initial procedure with the need for a parenchymal resection (for example, due to a recurrence pneumothorax or fistula formation) will cause the exclusion of the patient from the study. Patients may cancel their participation in the study at any time they wish, without giving reasons for the decision. In addition, the principal investigator may exclude a patient from the study if the continuation of the study compromises the patient’s well-being. The study cancellation will be documented in the eCRF and in the patient’s file, and all SAEs occurring from this point must be followed up. Premature discontinuation of the entire study will be done at the recommendation of the DSMB that the study be terminated for security reasons.

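### Ending participation after most thoracic reinterventions and after protocol violations contradicts the ITT analysis and the promised two-year follow-up of all patients, and selectively removes late outcome visits

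*Protocol article*

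**What the plan says.** Three sections of the protocol article bear on this.

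- **Dropout/exclusions** sets the rule: "The termination criteria of the study are defined as thoracic reintervention" (its examples are drainage, suction thoracentesis, and surgery for recurrence or for another reason), then the patient's wish to withdraw, "and violation of the protocol". Two exceptions follow. During the hospital stay after surgery, "a new or additional chest tube is not a termination criterion"; likewise "a pleural puncture for aspiration of pneumothorax or residual pneumothorax is not a termination criterion". After cancellation the only stated data collection is follow-up of SAEs.
- **Study procedure** says: "To assess the long-term effect of surgical intervention, all patients will be followed up for two years". Table 1 places SF-36, VAS and AEs/SAEs at V3, V4 and V5 (6, 12 and 24 months).
- **Statistical analysis** says: "The primary statistical analysis will be performed in the intention-to-treat (ITT) population". That set is all randomised patients in whom diagnostic thoracoscopy confirmed that a thoracoscopic operation is feasible. Nobody is removed for reintervention or protocol violation.

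**The concern.** The three statements cannot all be followed. A patient reoperated after discharge for a reason other than recurrence is in the ITT set and is owed two years of follow-up, yet leaves the study. The same applies to a protocol violator. The article does not define a violation, but the term could cover a PP patient who is given a resection or a WRPP patient who is not. For these patients the plan provides no 24-month visit at which recurrence would be established.

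A second group is those whose recurrence is drained or operated on after discharge. Their primary event has occurred, but their later SF-36 and VAS visits are cancelled. If one arm has more recurrences, it loses more of its worse-off patients, and its late means look better than they should.

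This is not a detail left to an analysis plan. The article states the rule positively, and an analysis plan cannot recover visits that were never held. The 5 % drop-out allowance does not clearly cover these losses: it is justified by painless visits and a young, healthy population, which argues against voluntary drop-out and says nothing about termination imposed by the protocol.

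**Working it through.** **Inputs.** From Sample size estimation: recurrence 8.6 % (PP) and 1.4 % (WRPP), two-sided Fisher's exact test at 0.05, 170 evaluable and 180 randomised per arm, 5 % drop-out. The documents give no rate for reinterventions or violations that end participation and no SF-36 decrement after recurrence, so both are assumed below.

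**1. The plan's own figure.** The two-proportion formula gives 143 per arm. With continuity correction, 143/4 × [1 + √(1 + 4/(143 × 0.072))]² = 169.6, so 170, as stated. Drop-out: 170/0.95 = 178.9, so 179 against the stated 180. Fully enumerated Fisher power at 170 per arm is 84.7 %. The sample size is not at fault.

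**2. Who loses what under the rule as written.**

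| Patient | Primary event | Later visits |
|---|---|---|
| Recurrence drained or operated on after discharge | Already occurred | SF-36 and VAS lost |
| Reintervention for another indication after discharge | Later recurrence recorded only if an SAE | Lost |
| Protocol violation | Later recurrence recorded only if an SAE | Lost |
| Added chest tube in index stay, or aspiration | Participation continues | Kept |
| Any patient, index-operation materials | – | Kept; counted at the end of surgery |

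**3. Recurrences that could cancel later visits.** PP: 180 × 0.086 = 15.5. WRPP: 180 × 0.014 = 2.5. These are upper limits. They require that every recurrence is treated by a reintervention that ends participation, and early enough to precede the visit in question.

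**4. Bias in late SF-36.** Let recurrence lower SF-36 by δ. With everyone observed, an arm's mean lies p × δ below the mean of its recurrence-free patients. If all patients with recurrence are missing, that reduction disappears, so the between-arm comparison shifts by (0.086 − 0.014) × δ = 0.072 × δ in favour of PP.
- δ = 5 (assumed): 0.072 × 5 = 0.36 points.
- δ = 20 (assumed): 0.072 × 20 = 1.44 points.

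**5. The primary comparison: loss unrelated to outcome.** Assumed loss per arm from 180, with Fisher power:

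| Loss | Evaluable per arm | Power |
|---|---|---|
| 5 % | 171 | 84.9 % |
| 10 % | 162 | 82.4 % |
| 15 % | 153 | 79.4 % |
| 20 % | 144 | 76.2 % |

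Loss of numbers alone does moderate harm.

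**6. The primary comparison: sensitivity to a few unobserved events.** Only about 15.5 + 2.5 = 18 events are expected. Fisher p-values with 180 per arm:
- 15 v 3: p = 0.006.
- 11 v 3 (four PP recurrences unseen): p = 0.053.
- 15 v 6 (against 15 v 3, three WRPP recurrences seen rather than missed): p = 0.070.

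This shows how fragile the result is. It does not predict that such losses will occur.

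**The case against.** The strongest defence is that the primary endpoint is largely protected. It is a binary event within 24 months, so a patient terminated because of a recurrence already has it. Under Assessment of safety, re-operation and inpatient hospitalisation are SAEs, and SAEs after cancellation must be followed up, so a later recurrence leading to either should still be recorded. The ITT definition does not drop terminated patients. SF-36 and VAS are secondary outcomes, analysed as exploratory. The article is also condensed, and the full protocol may say more about terminated patients.

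Much of this stands, and it rules out several stronger readings that a reader might draw:

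- **That any thoracic reintervention ends participation.** The two exceptions contradict this.
- **That 24-month recurrence status is unknown for everyone terminated.** The article does not say so. The gap is recurrences that are not SAEs, together with the missed visits.
- **That patients with recurrence vanish from the quality-of-life and cost comparisons.** Values collected before termination remain. Trocars and stapling magazines are counted at the operation, and Table 1 has no item for the cost of treating a recurrence, so no cost-bias figure is supported.
- **That crossover affects PP alone.** A WRPP patient who receives no wedge resection also departs from the protocol. The article links the bleeding and fistula risks of stapling to longer hospital stays, and how in-hospital reoperations other than for parenchymal resection are treated is unclear. The direction of differential loss in the primary outcome is therefore not established.

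What the defence does not remove is the contradiction. SAE reporting is no substitute for the 24-month visit, since a recurrence managed without admission or re-operation need not be an SAE. Details in a fuller document could explain the rule, but the rule as published still ends the visits.

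**Conclusion.** The point holds in a limited form. The termination rule contradicts both the ITT primary analysis and the two-year follow-up of all patients. It leaves patients reoperated for another indication, and protocol violators, without a planned 24-month visit. Their number cannot be derived from the article. The effect on power is moderate if the loss is unrelated to outcome, but with about 18 expected events a few recurrences missed in one arm could change the conclusion.

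The late SF-36 bias has a known direction (favouring PP) if recurrence is commoner under PP and lowers quality of life. The 0.36 to 1.44 points are a ceiling: they rest on the planned recurrence rates, on an assumed decrement of 5 to 20 points, and on every recurrence ending participation before the visit analysed. VAS is exposed in the same way, but no size can be given.

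A neighbouring clause deserves attention in the same revision. In-hospital reoperation with parenchymal resection ("for example, due to a recurrence pneumothorax or fistula formation) will cause the exclusion of the patient from the study") raises the separate question of whether such a recurrence is still counted as a primary event. The article does not say, and nothing above depends on the answer.

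**What to change.** Reconcile Dropout/exclusions with Statistical analysis and Study procedure:

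1. State that only withdrawal of consent for follow-up ends data collection.
2. Record each reintervention and protocol deviation with its date and reason.
3. Keep all other patients in the scheduled V3 to V5 assessments: recurrence status, SF-36, VAS, AEs/SAEs.
4. Analyse them in the arm to which they were randomised. A per-protocol set may serve as a sensitivity analysis only.

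This concerns data collection and analysis. It leaves the clinical handling of reinterventions untouched.

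The cost is an amendment and the remaining routine visits for a limited number of patients, with no new procedures; contact is already required for SAE follow-up. The article reports 61 of the planned 360 patients randomised by 22 January 2015, so at that stage a change would cover most of the trial. Visits already missed cannot be restored.

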### Endpoints

The primary endpoint is PTX recurrence within the first 24 months after operative treatment. PTX recurrence is defined as postoperative lung collapse documented by chest X-ray. Secondary endpoints are morbidity, mortality, and postoperative convalescence. Morbidity will be differentiated between general and surgical complications. In addition, postoperative pain (at rest/under exertion) will be determined by the visual analogue scale (VAS). Postoperative quality of life will be captured by using the SF-36 questionnaire.

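### A post-randomisation exclusion triggered by in-hospital reoperation conflicts with the endpoint and ITT definitions, and leaves open whether the recurrences behind it are counted

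*Protocol article*

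**What the plan says.** Three sections of the protocol article bear on this.

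- **Endpoints.** "The primary endpoint is PTX recurrence within the first 24 months after operative treatment", and "PTX recurrence is defined as postoperative lung collapse documented by chest X-ray". The window opens at the operation; the index hospital stay is not carved out.
- **Statistical analysis.** "The primary statistical analysis will be performed in the intention-to-treat (ITT) population". The set is then defined: "This analysis set includes all randomized subjects for which a diagnostic thoracoscopy has confirmed that thoracoscopic operation is feasible". Thoracoscopic feasibility is the only condition.
- **Dropout/exclusions.** Thoracic reintervention, including surgery for recurrence, is a termination criterion. Some in-hospital measures are exempt: "During the hospital stay after surgery (and thus after randomization) a new or additional chest tube is not a termination criterion", and the same holds for a pleural puncture. The section also sets a rule for exclusion from the study: an in-hospital reoperation "with the need for a parenchymal resection (for example, due to a recurrence pneumothorax or fistula formation) will cause the exclusion of the patient".

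No section says how a patient excluded in this way enters the primary analysis.

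**The concern.** The exclusion comes after randomisation and can be set off by the primary outcome itself. It also selects on severity: an early collapse managed with a tube or a puncture leaves the patient in the study, while one that leads to a lung resection takes the patient out.

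The trigger is not neutral between arms either. Under Study procedure, an apical wedge resection is what the experimental arm receives and the control arm does not. A PP patient who later needs a resection may be one in whom pleurectomy alone failed. If such patients leave the analysis, the two arms are no longer compared as randomised.

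Few events are expected, so a handful of patients can decide the result. The direction matters as well: the abstract says that a finding of equivalence could spare patients lung resections. A rule that drops recurrences mostly from PP would push the result that way.

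**Working it through.** **Inputs from the protocol article.** Planning rates: "8.6 % for patients under pPTX and 1.4 % for patients under WRPP, a difference of 7.2" percentage points (the first group, written there as pPTX, is pleurectomy alone). Test: two-sided Fisher's "exact test at significance level 0.05". 170 evaluable patients per arm for 80% power, 5% dropout, 180 per arm, 1:1 allocation.

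**1. Reproducing the stated sample size.** With p1 = 0.086, p2 = 0.014 and mean 0.05:

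n = [1.960·√(2·0.05·0.95) + 0.842·√(0.086·0.914 + 0.014·0.986)]² / 0.072² = 142.7, so 143.

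With the continuity correction, n' = (n/4)·[1 + √(1 + 4/(n·0.072))]² = 169.3, so 170, as stated. Dropout: 170/0.95 = 178.9, so 179; the article uses 180. Full enumeration of the two-sided Fisher test at 170 per arm gives a power of 84.7%, so the stated 80% is slightly conservative.

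**2. Where the events are expected.** PP: 170 × 0.086 = 14.6. WRPP: 170 × 0.014 = 2.4. Of 17.0 in total, 14.6/17.0 = 86% are in PP.

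**3. Effect of removing failures.** The article gives no rate of in-hospital reoperation with resection, so the shares below are assumptions. If a fraction a of an arm's patients are failures who are then excluded, they leave numerator and denominator: the analysed rate is (p − a)/(1 − a) and the analysed number is 170·(1 − a).

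| Assumed exclusions, PP v WRPP | Analysed rates | n, PP v WRPP | Exact Fisher power |
|---|---|---|---|
| none | 8.6% v 1.4% | 170 v 170 | 84.7% |
| 2% v 0% | 6.7% v 1.4% | 167 v 170 | about 70% |
| 3% v 0% | 5.8% v 1.4% | 165 v 170 | about 57% |
| 3% v 0.5% | 5.8% v 0.9% | 165 v 169 | about 71% |

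For the second row: (0.086 − 0.02)/0.98 = 0.0673, and 170 × 0.98 = 166.6. The loss is 170 × 0.02 = 3.4 PP patients.

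**4. The same check by share of failures lost.** If a share f of PP failures is excluded and none from WRPP, power is 83.0% (f = 10%), 73.5% (20%), 61.7% (30%) and 34.4% (50%). If the same share is lost in both arms, it is 85.6%, 80.2%, 74.0% and 56.5%. These values need not fall smoothly, because the Fisher test is discrete.

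**5. One illustrative (invented) data set.** 12/170 v 3/170 gives p = 0.031. Excluding three PP failures gives 9/167 v 3/170, p = 0.084.

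**6. Fistula.** A fistula without X-ray-documented collapse is not a primary event. Excluding such a patient costs one patient's 24-month outcome; it does not remove a failure.

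**The case against.** The best defence is that the Dropout/exclusions section governs participation, not analysis. The same section lets the principal investigator exclude a patient on grounds of well-being, then speaks of study cancellation with further SAE follow-up. Exclusion may therefore mean only that visits stop. The ITT definition, taken alone, keeps these patients. The recurrence precedes the exclusion. Re-operation is an SAE entered in the eCRF, and primary outcomes and SAEs are monitored for every patient, so the event should be on record and countable.

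This reading is possible, and it rules out a stronger claim that a reader might make: that the plan definitely deletes these failures from the primary analysis. The text does not establish that. But it does not exclude it either, and a full protocol that settles the matter is not shown. The exclusion itself is stated outright and not left open, so its clash with the other two sections is in the published text.

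Two further inferences go too far. The first is that the losses fall mainly on PP. That extends 24-month planning rates to early reoperations, for which no rate is given, and the rule also covers fistula, where the Rationale says stapling raises the risk; those exclusions may fall more on WRPP. Nor would WRPP fistula exclusions simply reverse the bias, since no primary event is lost with them.

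The second concerns size. Lowering the rates but leaving 170 per arm gives powers of 63%, 48% and 63% for the three scenarios. That contradicts the premise that the excluded patients also leave the denominator.

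**Conclusion.** The point stands as a conflict between Endpoints, Statistical analysis and Dropout/exclusions that has to be reconciled before analysis. Followed literally, the exclusion removes primary events after randomisation and, for fistula, the 24-month follow-up, in a way that may differ by arm.

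Losing recurrences would probably bias towards no difference. This rests on the planning rates and is not something the article states. The size cannot be fixed from the article. Under the assumed rates, power falls from 84.7% to between about 57% and 71%, but stays near 83% if only 10% of PP failures are lost. The practical weight therefore depends on how often such reoperations occur. The matter still belongs among the required corrections, because it decides who is counted for the primary endpoint.

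**What to change.** Reconcile the three sections by stating that:

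- reoperation or early termination does not remove a patient from the ITT set;
- any X-ray-documented recurrence before or at the reoperation is a primary event in the randomised arm;
- a patient reoperated for fistula without recurrence stays in outcome follow-up to V5 and in the ITT analysis.

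Apply this to the patients already randomised (61 at the date given in the article). The SAE and eCRF records should identify any who were excluded, since re-operation is a reportable SAE.

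The cost is wording, plus retrieval of outcomes for any such patients. It needs no additional patients or procedures. The change concerns counting and follow-up only; clinical management is unchanged.
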